### Outcome measures

The primary outcome is a composite adverse maternal outcome including maternal neurological, haematological, cardiorespiratory, hepatic and renal complications and death. We prioritised the outcomes for clinical importance using a Delphi survey of researchers and clinicians. Prior to the analysis, after discussion with the independent Study Steering (SSC) and Data Monitoring (DMC) Committees, we included delivery before 34 weeks as a component of maternal composite outcome to minimise bias due to treatment paradox [23]. The secondary outcome is a composite adverse fetal outcome (Table 3).

**Table 3 Tab3:** Components of the maternal and fetal composite outcomes

Outcome	Definition
Maternal outcomes	
Mortality	Maternal death at any time in pregnancy after delivery until discharge
Hepatic dysfunction	INR >1.2 indicative of DIC in the absence of treatment with warfarin. (DIC is defined as having both abnormal bleeding and consumptive coagulopathy (i.e. low platelets, abnormal peripheral blood film, or one or more of the following: increased INR, increased PTT, low fibrinogen, of increased fibrin degradation products that are outside normal non-pregnancy ranges).)
Hepatic haematoma or rupture	Blood collection under the hepatic capsule as confirmed by ultrasound or laparotomy
Glasgow coma score <13	From the GCS scoring system [39]
Stroke	Acute neurological event with deficits lasting longer than 48 h
Cortical blindness	Loss of visual acuity in the presence of intact papillary response to light
RIND	Cerebral ischaemia lasting longer than 24 h but less than 48 h revealed through clinical examination
Retinal detachment	Separation of the inner layers of the retina from the underlying RPE (choroid) and is diagnosed by ophthalmological examination
Acute renal insufficiency	For women with an underlying history of renal disease: defined as creatinine >200 μM; for patients with no underlying renal disease: defined as creatinine >150 μM
Dialysis	Including haemodialysis and peritoneal dialysis
Transfusion of blood products	Includes transfusion of any units of blood products: FFP, platelets, RBCs, cryo or whole blood
Positive ionotropic support	The use of vasopressors to maintain a systolic blood pressure >90 mmHg or mean arterial pressure >70 mmHg
Myocardial ischaemia/infarction	ECG changes (ST segment elevation or depression) without enzyme changes and/or any one of the following: (1) development of new pathologic Q waves on serial ECGs. The patient may or may not remember previous symptoms. Biochemical markers of myocardial necrosis may have normalised, depending on the length of time that has passed since the infarct developed. (2) Pathological findings of an acute, healed or healing MI. (3) Typical rise and gradual fall (troponin) or more rapid rise and fall (CK-MB) of biochemical markers of myocardial necrosis with at least one of the following: (a) ischaemic symptoms; (b) development of pathologic Q waves on the ECG; (c) ECG changes indicative of ischaemia (ST segment elevation or depression) or (d) coronary artery intervention (e.g. coronary angioplasty)
Require >50% oxygen for greater than 1 h	Oxygen given at greater than 50% concentration based on local criteria for longer than 1 h
Intubation other than for caesarean section	Intubation maybe by ventilation, electrical impedance tomography or continuous positive airway pressure
Pulmonary oedema	Clinical diagnosis with x-ray confirmation or requirement of diuretic treatment and SaO_2_ <94%
Postpartum haemorrhage	>1 L of blood loss after delivery
Early preterm delivery	Delivery at gestational age of less than 34 weeks
Fetal outcomes	
Perinatal or infant mortality	Death of a fetus or neonate. Infant mortality is the death of a child less than 1 year of age
Bronchopulmonary dysplasia	Oxygen requirement at 36 weeks’ corrected gestation unrelated to an acute respiratory episode
Necrotising enterocolitis including only Bell’s stage 2 or 3	Evidence of pneumotosis intestinalis on abdominal x-ray and/or surgical intervention
Grade III/IV intraventricular haemorrhage	Bleeding into the brain’s ventricular system, where the ventricles are enlarged by the accumulated blood or bleeding extends into the brain tissue around the ventricles
Cystic periventricular leukomalacia	Softening and necrosis in the hemispheric white matter in newborns that may result from impaired perfusion at the interface between the ventriculopetal and ventriculofugal arteries
Stage 3–5 retinopathy of prematurity	Abnormal blood vessel development in the retina of the eye, where blood vessel growth is severely abnormal, where there is a partially or totally detached retina
Hypoxic ischaemic encephalopathy	Apgar score ≤5 at 10 min and/or pH 7.00 in the first 60 min of life and/or base deficit ≥−16 in the first 60 min associated with an abnormal consciousness level (lethargy, stupor or coma) and seizures and/or poor/weak suck and/or hypotonia and/or abnormal reflexes

Adapted from the PIERS study

*INR* international normalised ratio, *DIC* disseminated intravascular coagulation, *PTT* partial thromboplastin time, *GCS* Glasgow Coma Scale, *RIND* reversible ischaemic neurologic deficit, *RPE* retinal pigment epithelium, *FFP* fresh frozen plasma, *RBCs* red blood cells, *cryo* cryoprecipitate, *ECG* electrocardiography

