### Study design and conduct

PREP is a prospective, multicentre, observational cohort study involving secondary and tertiary care obstetric units in England and Wales. All consecutive women with a suspected or confirmed diagnosis of pre-eclampsia before 34 weeks of gestation will be approached to take part in the study by research midwives and clinicians in antenatal clinics, wards, day assessment units and delivery suites. Clinicians managing the women will be requested to complete the Clinicians Management Plan at baseline to assess the reasons for planned management. The predictors evaluated in the PREP prediction model are routinely performed as part of standard clinical practice in women admitted with early-onset pre-eclampsia. The PREP study does not influence the management of these patients.

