### Candidate variables for inclusion in the model

Candidate predictor variables will be obtained from patient demographic characteristics and from clinical assessment including clinical history, examination and investigations. The predictors will be clearly defined and standardised to ensure reproducibility and enhance generalisability and application of study results to practice. Data will also be collected on any interventions applied between recruitment and outcome onset that may modify the outcome.

We will choose the candidate predictors a priori to be considered in the prediction model, based on the most promising predictor variables as identified with our previous systematic review [17–22]. The full list of variables to be evaluated for prediction of maternal and fetal outcomes is provided in Table 2.

**Table 2 Tab2:** List of candidate predictor variables to be evaluated in the PREP study

Maternal characteristics Maternal age at diagnosis (years) Gestational age at diagnosis (weeks) Number of fetuses in pregnancy at time of consent (1, 2, 3)
History Summary score for medical history—1 point for each of the following: pre-existing hypertension, renal disease, diabetes mellitus, autoimmune disease, previous history of pre-eclampsia (0, 1, 2 or more)
Symptoms Headache and/or visual disturbance (yes/no) Epigastric pain, nausea and/or vomiting (yes/no) Chest pain and dyspnoea (yes/no)
Bedside examination and tests Systolic blood pressure (mmHg, highest measurement over 6 h) Diastolic blood pressure (mmHg, highest measurement over 6 h) Clonus (yes/no) Exaggerated tendon reflexes (yes/no) Abnormal oxygen saturation (<95% on air) (yes/no) Urine dipstick (0, 1+, 2+, 3+, 4+ or more)
Laboratory tests Haemoglobin (g/L) Platelet count (× 10^9^/L) ALT (IU/L) Serum uric acid (μmol/L) Serum urea (mmol/L) Serum creatinine (μmol/L) Urine protein-creatinine ratio (PCR) (mg/mmol)
Management at baseline Administration of oral and/or parenteral anti-hypertensives (ongoing or commenced within 1 day of diagnosis) (yes/no) Administration of magnesium sulphate (commenced before or within 1 day of diagnosis) (yes/no)
Additional factors for fetal model only Uterine artery Doppler (normal/abnormal) Liquor volume (normal/abnormal) CTG findings (normal/abnormal) Estimated fetal weight <10th centile (yes/no)

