### Sample size considerations

From our systematic reviews [17], 20% of women with early-onset pre-eclampsia are expected to have adverse maternal outcomes at any time before discharge. Rules of thumb for fitting multivariate models suggest about 10 events for every variable are required to reduce issues with overfitting, and we will work within this constraint [24–26]. We initially planned to examine 10 predictor variables and hence planned to recruit 500 women. However, the event rate was lower than predicted, so we revised our plan to recruit sufficient women to obtain 100 events. Subsequent to the inclusion of delivery before 34 weeks as a component of the composite outcome, we revised our plan to include 22 candidate predictor variables, which was approved by the independent study Committees.

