#### Model development, apparent performance assessment and internal validation

The predictors of adverse maternal outcomes will be identified to develop and externally validate a simple, interpretable and clinically applicable prediction model with face validity. We will use a transparent process that implements appropriate statistical methods and adheres to current methodological recommendations.

A backwards selection procedure will be used to decide which of the candidate predictor variables should be included in the final prediction model (with *p* < 0.15 taken conservatively to warrant inclusion). Continuous variables will be kept as continuous in the model (rather than dichotomising), to avoid a loss of power [27, 28]. Non-linear trends will also be considered using the multivariable fractional polynomial procedure [29, 30], which uses multivariable models to eliminate weaker predictors and identify transformations of continuous predictors that best predict outcome. Large amounts of missing variable data are not expected, but some will inevitably occur, with not all patients providing all variables of interest. Multiple imputation will be used to impute, with 5 imputations, under a missing at random assumption, missing values so as to avoid excluding patients from the analysis [27].

For survival analysis, failure event is defined as an adverse outcome or delivery occurring before 34 weeks of gestation. We will use a flexible parametric survival model via the Royston-Parmar approach [31–33], with the cumulative baseline hazard scale modelled using restricted cubic splines. The number of knots will be chosen by visual inspection. For the binary adverse maternal outcome by discharge, a logistic regression-modelling framework will be undertaken with the logit probability of an adverse outcome being the response variable.

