Ideally, to develop a prediction model, we would like to observe outcomes in a cohort of women who receive no clinical management at all to be able to predict the likelihood of an adverse outcome independent of clinical management. Clearly, this is unethical and all women who present with pre-eclampsia receive clinical management, but such clinical decisions also affect maternal outcomes. Thus, in the development of our prediction model, we must recognise the importance of accounting for current clinical management; however, this is currently an under-researched methodological issue. By including effective treatment measures such as use of anti-hypertensives and magnesium sulphate predictor variables, and delivery before 34 weeks as a component of the composite outcome, we plan to negate some of the bias arising from treatment paradox in prediction models [23].

There is no obvious single outcome measurement that determines clinical management in early-onset pre-eclampsia. As the risk of more than one outcome needs evaluation simultaneously, we have chosen a composite measure consisting of several complications [37]. The composite outcomes are constructed by including those components whose underlying biology is similar [38].

To show that the PREP prognostic model is valuable, it is not sufficient to show that it successfully predicts outcome in the initial development data even after having it being internally validated. We need evidence that the model performs well for other (external) patients. The resulting geographical and domain validation will enable us to assess the prognostic performance and the generalisability of the model.

Our prediction model plans to use rigorous statistical methods to develop the model and assess accuracy; undertake a formal validation in external datasets (PIERS and PETRA); use unambiguous definitions of predictors and reproducible measurements using methods available in clinical practice; adjust for current clinical management; obtain input from patient focus groups and produce personalised estimates of risk, which enable patients and clinicians to make more informed decisions on management aspects like continuing the pregnancy or delivery of a preterm baby.

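### The reported risk of maternal complications would in fact be the risk of a complication or of delivery before 34 weeks for any reason, and should be named and broken down that way

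*Protocol article*

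**What the plan says.** - **Outcome.** Under Outcome measures, the article states that "we included delivery before 34 weeks as a component of maternal composite outcome to minimise bias due to treatment paradox". Table 3 defines the component as "Delivery at gestational age of less than 34 weeks" and names no indication.
- **Survival model.** Under model development, the "failure event is defined as an adverse outcome or delivery occurring before 34 weeks of gestation", again without an indication.
- **Predictors.** Table 2 places uterine artery Doppler, liquor volume, CTG findings and estimated fetal weight below the 10th centile under "Additional factors for fetal model only". Sample size considerations says "we revised our plan to include 22 candidate predictor variables" once delivery had joined the composite.
- **Description and use.** The abstract's closing paragraph presents the output as a quantified risk of maternal complications at several time points. The end of the Discussion says the personalised estimates should help patients and clinicians decide whether to continue the pregnancy or deliver.
- **Reasons for management.** Clinicians "complete the Clinicians Management Plan at baseline to assess the reasons for planned management" (Study design and conduct). The section on candidate variables adds that interventions between recruitment and outcome onset will be recorded if they may modify the outcome.

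**The concern.** A pregnancy with early-onset pre-eclampsia may end before 34 weeks because the mother deteriorates, because the fetus is compromised, or because labour starts. The composite counts all three alike. A woman with no complication who is delivered for an abnormal CTG is a maternal event, and the finding that led to her delivery cannot enter the model.

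What is at stake is the meaning of the predicted number. The Background frames the clinical decision as fetal benefit from prolonging pregnancy set against maternal risk. If the maternal figure already contains deliveries made for the fetus, part of the fetal side is counted on the maternal side, and a reader who takes the label literally will read the figure as too high for maternal harm. The C-statistic and calibration will likewise describe prediction of the mixture and will not show how well the model predicts maternal complications.

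**Working it through.** **1. The plan's own sample size.** Inputs from Sample size considerations: 10 predictors, 10 events per variable, and "20% of women with early-onset pre-eclampsia are expected to have adverse maternal outcomes at any time before discharge". Events = 10 × 10 = 100. Women = 100 / 0.20 = 500. This matches the stated 500.

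**2. Are the fetal findings really outside the maternal model?** Entries in Table 2 without the fetal-only block: maternal characteristics 3, history 1, symptoms 3, bedside 6, laboratory 7, management 2. Sum = 3 + 1 + 3 + 6 + 7 + 2 = 22, exactly the stated number of candidates. Adding the four fetal findings would give 26. The exclusion is therefore deliberate.

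**3. Following one case through the definitions.** Take a woman with no maternal complication who is delivered before 34 weeks for an abnormal CTG.
- Table 3: she meets the early preterm delivery component, so she is an event for the logistic model.
- Survival model: she is a failure at delivery.
- Table 2: CTG is not a candidate. Gestational age and number of fetuses are candidates and may bear on early delivery, but neither measures fetal compromise.
- Abstract: her event contributes to what is called maternal complication risk.

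**4. How large could the delivery part be?** The documents give no split by indication, so this is an illustration.
- Events needed at 10 per variable: 22 × 10 = 220.
- Assume that the revised target of 100 events, set before delivery was added, refers to complications. Delivery alone then supplies 220 − 100 = 120 events, and 120 / 220 = 54.5%.
- Assume that a share s of those 120 deliveries was for fetal reasons only:

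| s | Events (120 × s) | Share of 220 |
|---|---|---|
| 10% | 12 | 5.5% |
| 30% | 36 | 16.4% |
| 50% | 60 | 27.3% |

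Spontaneous deliveries would come on top.

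**5. What a separate analysis could support.**
- Complications alone: 100 / 22 = 4.5 events per variable. At 10 per variable, 100 events support 100 / 10 = 10 predictors.
- Composite without the fetal-only deliveries of step 4: (220 − 12) / 22 = 9.5 down to (220 − 60) / 22 = 7.3 events per variable.

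Both fall below the plan's rule, which limits what the supplementary analysis can be.

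**The case against.** **The treatment paradox does not depend on indication.** The Background calls delivery the only known cure, and the Discussion says clinical decisions affect maternal outcomes. A delivery for the fetus can also avert a maternal complication. The choice was made before analysis, after discussion with the independent committees, and the Discussion claims to remove only some of the bias. This stands. A reader might infer that the composite is wrong because the rationale covers only deliveries done to protect the mother, but the article sets no such limit. Treating other deliveries as competing events would also bring part of the bias back.

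**The composite does not plainly break its own principle.** The Discussion says "The composite outcomes are constructed by including those components whose underlying biology is similar". One might read this as contradicted by fetal-indication delivery. However, the Background links hypertensive disease in pregnancy to about 20% of stillbirths, so fetal compromise can belong to the same disease process. The conflict is arguable, and the point does not rest on it.

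**Indication may be recorded.** It is tempting to say that reasons are sought only at baseline. A condensed article cannot show that, and it also plans to record later interventions.

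**The analysis plan may hold sensitivity analyses.** It may, and their absence here is no fault in itself. The point rests on two things this document does state: an all-indication outcome and a narrower description of the output.

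**External validation will reveal miscalibration.** It may show that calibration differs in the other cohorts. Without a breakdown by component, it cannot show whether a different mix of deliveries is the reason.

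**Conclusion.** The point holds as one of naming and interpretation. As written, the models estimate the risk of a maternal complication or of delivery before 34 weeks for any reason, while the article presents this as maternal complication risk and intends it to guide continuation of pregnancy.

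The structure follows directly from Tables 2 and 3 and the failure-event definition. The size does not. The 55% delivery-only share assumes 100 complications and exactly 220 events, and the 5% to 27% fetal-only share further assumes that 10% to 50% of those deliveries were for fetal reasons. A reader might go on to infer a specific loss in C-statistic or a fixed number of risk points that are not maternal. The documents contain neither the indication split nor the discrimination for each type of event, and a constant fetal share would in any case hold only on average across women. The primary composite need not change.

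**What to change.** 1. **Label.** Keep the composite as primary and call it *maternal complication or delivery before 34 weeks for any reason* wherever a predicted risk is reported, including the abstract and any risk tool. This costs only wording.
2. **Separate the components.** Pre-specify, for both models, a supplementary report of C-statistic and calibration separately for maternal complications and for delivery without complication. A model built for the composite will overpredict each component alone by construction, so the calibration display should show the observed proportion of each component across levels of predicted composite risk.
3. **Use indication where available.** If the indication is recorded or can be taken from the notes, add a version in which only maternal-indication or mixed deliveries are failures, with other deliveries as a competing event in the survival model.

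Costs and limits to state:
- Events fall below 10 per variable for 22 predictors (step 5 of the working). The supplementary analysis should therefore evaluate the developed model or use fewer predictors, and should not repeat the full selection.
- Mixed indications, and women with both a complication and early delivery, need a coding rule. It may have to be applied retrospectively, since recruitment appears to have been under way when the outcome changed.
- Treatment paradox partly returns in the indication-based version, so it is supportive only.

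None of this touches clinical decisions on delivery.

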### Objectives

The primary objectives are to develop and internally validate a prediction model in women admitted with early-onset pre-eclampsia from 20 weeks and 0 day to 33 weeks and 6 days of gestation, for assessment of the risk of adverse maternal outcomes at 48 h and by discharge. The 48 h of time interval was chosen to reflect the time recommended for delivery after administration of steroids to lower risks of respiratory distress in newborns. This time period is also considered to be the optimal duration to make decisions on timing and place of delivery and consider in utero transfer to a tertiary care unit if needed. The model will be externally validated in two independent datasets of patients with a diagnosis of early-onset pre-eclampsia. Our secondary objective is to assess the risk of adverse fetal and neonatal outcomes at birth and at any time until discharge.

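### Two Table 3 outcome definitions are wrong as written: the HIE base-deficit limit excludes almost no infant, and the maternal intubation row lists things that are not intubation

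*Protocol article*

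**What the plan says.** Both rows are in Table 3 of the protocol article, under Outcome measures.

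- **HIE, fetal outcomes.** The row opens with three perinatal criteria. The first two are "Apgar score ≤5 at 10 min and/or pH 7.00 in the first 60 min of life and/or", and the third is "base deficit ≥−16 in the first 60 min associated with an abnormal consciousness level". The neurological signs follow: "lethargy, stupor or coma) and seizures and/or poor/weak suck and/or hypotonia and/or abnormal reflexes". The fetal composite is the secondary outcome.
- **Intubation, maternal outcomes.** The label restricts the row to intubation for reasons other than caesarean section. The definition is "Intubation maybe by ventilation, electrical impedance tomography or continuous positive airway pressure". This row is a component of the primary composite.

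Nothing elsewhere in the article corrects or qualifies either row.

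**The concern.** In the HIE row, the perinatal criteria are there to restrict the diagnosis to infants with evidence of an insult around birth. A limit that almost everyone meets, joined to the others by and/or, removes that restriction. An assessor who applies the row literally would accept an infant on lethargy plus, say, weak suck. An assessor who guesses the intention would require severe acidosis, a low Apgar score or a low pH. In a multicentre study the classification would then depend on who reads the row.

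In the intubation row, label and definition disagree. A woman supported by continuous positive airway pressure (CPAP) without a tube is an event under the definition and not under the label. This matters more in principle, because the row feeds the composite on which both maternal prediction models are built.

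**Working it through.** The plan states no figure to reproduce here. The check is one of logic, with illustrative probabilities for the HIE limit.

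**HIE: the logic**

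Let A be the Apgar criterion, P the pH criterion, B the base-deficit criterion and S the required neurological signs. The natural reading of the row is HIE = (A or P or B) and S. If B is always true, (A or P or B) is always true, and HIE = S. If the signs are instead attached only to the base-deficit criterion, the row is A or P or (B and S). With B always true, the signs alone still suffice.

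**HIE: how often B is true**

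Inputs: the limit of −16, from Table 3. The article gives no distribution of base deficit, so the following are assumptions: normal, in mmol/L, positive for acidosis, mean *m* of 2, 5, 8 or 12 and SD *s* of 3, 5 or 6. The row prints no unit, so mmol/L is also assumed.

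- As printed: P(deficit ≥ −16) = 1 − Φ((−16 − *m*)/*s*). The lowest value is at *m* = 2, *s* = 6: 1 − Φ(−3) = 0.99865.
- If deficit was meant as excess: P(excess ≥ −16) = P(deficit ≤ 16) = Φ((16 − *m*)/*s*). At *m* = 8, *s* = 6 this is Φ(1.33) = 0.909. At *m* = 12, *s* = 6 it is Φ(0.67) = 0.748.
- Sign corrected: P(deficit ≥ 16) = 1 − Φ((16 − *m*)/*s*).

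| Assumed mean deficit (SD 3 to 6) | Deficit ≥ −16, as printed | Read as excess ≥ −16 | Deficit ≥ 16, corrected |
|---|---|---|---|
| 2 | 99.87% to 100% | 99.0% to 100% | <0.1% to 1.0% |
| 5 | 99.98% to 100% | 96.7% to 99.99% | <0.1% to 3.3% |
| 8 | >99.99% | 90.9% to 99.6% | 0.4% to 9.1% |
| 12 | >99.99% | 74.8% to 90.9% | 9.1% to 25.2% |

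The limit runs the wrong way on both readings. As a base deficit it screens out almost nobody. As a base excess it selects the less acidotic infants.

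On the base-deficit reading the direction of the error is fixed. Every infant with a deficit of at least 16 also has one of at least −16, so the literal rule can only add HIE cases to the corrected rule.

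**Intubation: label against definition**

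| Item in the definition | Is it intubation? |
|---|---|
| Ventilation | Not necessarily; it can be given without a tube |
| Electrical impedance tomography | No; it is an imaging and monitoring method |
| Continuous positive airway pressure | No; it can be given without a tube |

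For a woman to become an event in the by-discharge composite solely through this wording, three things must hold. She receives CPAP or non-invasive ventilation. She is not intubated. She has no other component, including more than 50% oxygen for over 1 h, pulmonary oedema and delivery before 34 weeks. In the survival model her event time could also move earlier, if the support precedes another component. The article gives no frequency for any of these.

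**The case against.** The strongest case on the other side is that both faults are drafting slips whose intent is obvious. Nobody would diagnose HIE in a well infant, because the row still demands altered consciousness and further signs. HIE also belongs to a secondary composite, and both models described under Statistical analysis are maternal. No site would count a woman for having imaging. Many women on CPAP would be events anyway through the overlapping components. Whether non-invasive support belongs in the composite is a choice of clinical content, and listing it openly would leave the count unchanged.

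Most of this stands, and it limits the consequence. It does not make the rows correct. The printed threshold is wrong on either reading, and a definition that contradicts its label leaves the choice to each assessor.

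A reader might infer more than the document supports:

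- **That Table 3 cannot be applied, or that nearly every infant would be labelled HIE.** Nearly every infant meets the base-deficit limit, not the full definition. The rows can be applied; taken literally, they classify by the wrong rule.
- **That HIE would be over-counted by a stated share, tied to gestational age.** The article does not say how often infants in this cohort show the neurological signs without acidosis, so any such share would be a guess.
- **That the pH criterion is also faulty because it shows no inequality.** A symbol may have been lost in conversion of the text, so no weight is placed on it.
- **That mortality is defined beyond follow-up.** The row reads "Death of a fetus or neonate. Infant mortality is the death of a child less than 1 year of age", while the Objectives set the window as "adverse fetal and neonatal outcomes at birth and at any time until discharge". The second sentence of the row can be read as explaining a term, with the Objectives fixing when deaths count. Read so, the two agree. At most, a clarification that deaths count until discharge would help.

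**Conclusion.** Two rows are wrong as written. The HIE limit has the wrong sign and voids the Apgar and acidosis screen in a secondary outcome. The intubation row contradicts its own label in the primary composite. These are wording corrections, not failures of design.

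The size is known only for the HIE limit itself: at least 99.8% of infants meet it as printed under every assumed distribution, against under 0.1% to 25% once corrected. This rests on the assumed normal distributions and applies to infants with a base deficit measured in the first hour. The effect on the number of HIE cases, fetal composite events or maternal composite events cannot be calculated from the document. For the maternal composite it is diluted by overlapping components, delivery before 34 weeks among them.

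**What to change.** Make two edits to Table 3 before any outcome is classified:

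1. **HIE row.** Change the limit to a base deficit of at least 16 mmol/L, or equivalently a base excess of −16 or lower, and print the unit.
2. **Intubation row.** Delete the imaging term and make label and definition agree. Either restrict the row to tracheal intubation, or name CPAP and other non-invasive support explicitly as counted components. The study team should choose between these on clinical grounds, without sight of the model results.

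Carry the same wording into the case report form guidance and into the outcome coding for the external validation cohorts, as far as their data allow. The cost is two table edits and no new data, and the downside is negligible. If some outcomes have already been classified, the HIE and intubation records would need re-checking against the edited rows.
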